### Statistical methods

Each of the two active treatment groups will be compared separately with the control group for 12-month prevalence of atypical hyperplasia and cellular proliferation (Ki-67), considered as two distinct endpoints. The comparison will be based on Pearson’s Chi-square test. A secondary analysis will be carried out within a Generalized Estimating Equations (GEE) logistic regression modeling approach. Such analysis will incorporate baseline and 12-month measurements, and will take into account possible correlation between the two assessments made within the same subject. Secondary endpoints considered in this study are represented by continuous variables. Treatment effect on their change over time will be investigated by means of covariance analysis (ANCOVA), possibly after suitable data transformations to achieve normal distributions.

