## Abstract

**Background:**

Despite positive results from large phase III clinical trials proved that it is possible to prevent estrogen-responsive breast cancers with selective estrogen receptor modulators and aromatase inhibitors, no significant results have been reached so far to prevent hormone non-responsive tumors. The Ductal Lavage (DL) procedure offers a minimally invasive method to obtain breast epithelial cells from the ductal system for cytopathologic analysis. Several studies with long-term follow-up have shown that women with atypical hyperplasia have an elevated risk of developing breast cancer. The objective of the proposed trial is to assess the efficacy and safety of a daily administration of nimesulide or simvastatin in women at higher risk for breast cancer, focused particularly on hormone non-responsive tumor risk. The primary endpoint is the change in prevalence of atypical cells and cell proliferation (measured by Ki67) in DL or fine needle aspirate samples, after 12 months of treatment and 12 months after treatment cessation.

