### Design overview

We are conducting a monoistitutional phase II, randomized, double blind, placebo controlled trial to assess the efficacy and the safety of a daily administration of nimesulide or simvastatin to change the expression of a large set of tissue and circulating surrogate endpoint biomarkers (SEBs) of breast carcinogenesis in women at higher risk of developing a hormone non-responsive (ER negative) breast cancer. The primary endpoint is the change in prevalence of atypical cells and cell proliferation (Ki-67), after 12 months of treatment. A total of 150 women were randomized: 50 per arm. Within the 3 treatment groups, subjects were stratified according to their hormonal status (premenopausal vs. postmenopausal ) and Ductal Intraepithelial Neoplasia (DIN)/Lobular Intraepithelial Neoplasia (LIN)/Atypical Hyperplasia(AH) vs. High genetic risk and centre. A schema of the trial design is presented in Figure 1.

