## Clinical evaluation and procedures

Date of birth, occupation, complete address and phone number, full details of family doctor; previous medical history; general physical examination, including anthropometric features; first or second degree family history of cancer; number of pack-years of cigarettes; alcohol consumption; concomitant medications.

Participants are assessed at baseline, 3, 6, 9, 12 and 24 months with clinical examination and blood safety tests. Mammography are performed at baseline, 12 and 24 months. DL are performed at baseline, 12 and 24 months in all subjects. In case of anatomical impediments to perform DL, this is substituted by a breast fine needle aspiration (FNA), preferably ultrasound-guided in the most dense area of the breast. Breast ultrasound is performed in premenopausal women at baseline, 12 and 24 months, in postmenopausal only if indicated by the study physician. Blood drawing for biomarkers and hormone measurements are done at baseline, 12 and 24 months. Intervention with nimesulide or simvastatin or placebo continues for 12 months or until the occurrence of a serious adverse event, including breast cancer. A detailed follow-up schema is illustrated in Table 1.

**Table 1 T1:** Follow-up procedures and main outcome measures

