## Statistical consideration

### Sample size

A total of 150 subjects are allocated in the three treatment groups: 50 for each treatment group. Within the 3 treatment groups, subjects are stratified according to their hormonal status (premenopausal vs. postmenopausal), DIN/LIN/AH vs. Genetic High Risk, and centre.

Such sample size yields a power of 80% to detect a reduction from an anticipated 50% 12-month prevalence of atypical hyperplasia and cellular proliferation (Ki-67) in the control arm to 25% in each of the treated arms. The specification of an alpha level of 0.1 and a one-sided test were used in the calculation of the power. Both choices of an alpha level greater than 0.05 and a one-sided test are justifiable in phase II studies, also considering that the study is interested in determining if the prevalence of atypical hyperplasia and cellular proliferation (Ki-67) is reduced by the investigated treatments. The planned sample size incorporates a correction for possibly inadequate tissue sampling in about 20% of study subjects.

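### The primary endpoint is worded as a change in prevalence, but the primary test is an unadjusted chi-square on 12-month prevalence: valid, but inconsistently described and giving up some precision

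*Protocol article*

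**What the plan says.** The Design overview states: "The primary endpoint is the change in prevalence of atypical cells and cell proliferation (Ki-67), after 12 months of treatment". The Abstract also speaks of a change and adds a second time point: "after 12 months of treatment and 12 months after treatment cessation".

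The Sample size section powers the trial on 12-month prevalence, 50% under control against 25% under each drug. The Statistical methods section keeps that quantity: "Each of the two active treatment groups will be compared separately with the control group for 12-month prevalence", for atypical hyperplasia and Ki-67 as two separate endpoints. It fixes the method: "The comparison will be based on Pearson’s Chi-square test". No baseline term and no stratum is mentioned.

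Baseline appears one step down: "A secondary analysis will be carried out within a Generalized Estimating Equations (GEE) logistic regression modeling approach", and "Such analysis will incorporate baseline and 12-month measurements, and will take into account possible correlation between the two assessments". No stratification factor is named there either.

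The information for adjustment is collected. Under Clinical evaluation and procedures, "DL are performed at baseline, 12 and 24 months in all subjects", with fine needle aspiration as the substitute. On randomisation, the Sample size section says that "subjects are stratified according to their hormonal status (premenopausal vs. postmenopausal), DIN/LIN/AH vs. Genetic High Risk, and centre".

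**The concern.** Two things do not fit together. First, the endpoint is defined as a change, while sizing and testing use the 12-month result alone. A reader cannot tell from the definition which quantity decides the trial. The Abstract's further time point after cessation has no analysis in the statistical sections.

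Second, the primary endpoint gets the least efficient analysis in the plan. The continuous secondary endpoints get ANCOVA on change, and the secondary analysis of the primary endpoints uses baseline. The deciding test uses neither baseline nor strata. Baseline atypia is not a stratification factor, so randomisation balances it only on average. The article itself calls the population heterogeneous in risk. With about 40 evaluable women per arm, chance baseline differences between arms can be sizeable, and an unadjusted test leaves that variation in the comparison.

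**Working it through.** **Inputs from the article.** 50 women per arm; 50% versus 25% at 12 months; one-sided alpha 0.10; stated power 80%; about 20% inadequate samples (all Sample size section). Evaluable per arm: 50 × 0.8 = 40.

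**Inputs assumed.** Baseline prevalence 50% in every arm, and a within-woman correlation φ between baseline and 12-month status of 0 to 0.5. The article gives neither. With 50% at baseline and 25% at 12 months, φ cannot exceed √(0.25/0.75) = 0.58, so 0.5 is close to the ceiling in a treated arm.

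**Step 1: reproduce the stated power.**
n = [z(0.90)·√(2·0.375·0.625) + z(0.80)·√(0.25 + 0.1875)]² / 0.25² = [1.2816 × 0.6847 + 0.8416 × 0.6614]² / 0.0625 = 32.9, so 33 per arm. With continuity correction it is 41, and 41 × 1.2 = 49.2, so 50.
Power at 40 per arm, with continuity correction: Φ[(0.25 − 0.025 − 1.2816 × 0.1083)/0.1046] = 79.5%. Without it: Φ[(0.25 − 1.2816 × 0.1083)/0.1046] = 85.6%; exact enumeration gives 85.9%.
The stated 80% reproduces for the planned unadjusted comparison.

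**Step 2: is the target the same?** Let B be the baseline and Y the 12-month prevalence in an arm.
Difference in change = (Y_drug − B_drug) − (Y_placebo − B_placebo) = (Y_drug − Y_placebo) − (B_drug − B_placebo).
Under randomisation the last bracket has expectation zero, so both comparisons have the same expected value. They differ in variance. Relative to the unadjusted comparison, the variance is about 1 − φ² when adjusted for baseline and about 2(1 − φ) for raw change.

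**Step 3: power at one-sided 0.10, 40 per arm** (20,000 simulated trials per row; the adjusted test is Cochran–Mantel–Haenszel, CMH, stratified on baseline status).

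| φ | Unadjusted | Baseline-adjusted | Raw change |
|---|---|---|---|
| 0 | 85.8% | 85.5% | 63.8% |
| 0.2 | 85.7% | 86.1% | 70.0% |
| 0.3 | 85.5% | 87.6% | 75.1% |
| 0.4 | 86.2% | 89.9% | 79.9% |
| 0.5 | 86.0% | 92.3% | 85.1% |

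The gain from adjustment runs from −0.3 points at φ = 0 to 92.3 − 86.0 = 6.3 points at φ = 0.5. Simulated type I error was 0.106 to 0.111 for the unadjusted test and 0.098 to 0.104 for the adjusted test, so the gain does not come from a looser test. A literal test of raw change has less power than the planned test over this whole range.

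**Step 4: size of a chance baseline imbalance.** Standard deviation of the baseline difference between two arms: √(2 × 0.25/40) = 0.112. A difference of 15 points or more in either direction has probability 2·[1 − Φ(0.15/0.112)] ≈ 0.18. At φ = 0.5 and equal spread at both visits, a 15-point imbalance moves the unadjusted 12-month difference by about 0.5 × 15 = 7.5 points, against a targeted 25.

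**Step 5: missing baseline samples.** Assume that 20% of baseline samples also fail, at random, and that the two results follow a latent normal model with correlation 0, 0.3, 0.5 or 0.7. For 50% prevalence at both visits, φ = (2/π)·arcsin(correlation) = 0, 0.19, 0.33 or 0.49.

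| Latent correlation | Unadjusted, all 40 | CMH, missing as its own category | CMH, complete cases |
|---|---|---|---|
| 0 | 86.1% | 85.3% | 78.8% |
| 0.3 | 85.8% | 85.8% | 80.0% |
| 0.5 | 85.6% | 86.8% | 81.4% |
| 0.7 | 85.9% | 90.0% | 85.9% |

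The gain from the strata cannot be computed, because the article does not say how prognostic they are.

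**The case against.** The best defence is that an unadjusted primary test with a baseline-using secondary model is a legitimate phase II choice. The Sample size and Statistical methods sections agree with each other, the test holds its level, and the stated power is met. Chance imbalance is already allowed for in the type I error. All of this stands. A reader might infer from the mismatch that the primary test answers a different question, is biased, or leaves the trial underpowered. Steps 1 and 2 show that the article does not support any of these.

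A second objection is that the gain is small and rests on an unknown correlation. Seven women moved from lavage to fine needle aspiration by 12 months, which may weaken it. This also stands, and it limits the claim to a range that includes no gain.

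A third is that failed baseline samples could cancel the gain. That is right for a complete-case analysis, which loses power or at best breaks even, but not when missing baseline is kept as its own category.

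A fourth is that a condensed article need not list model covariates. That is fair for the GEE: not naming the strata there does not show that they are left out. It does not protect the primary test, which the article names, and which as an unadjusted comparison has no place for covariates.

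A last one is sparseness. About 40 × 0.50 + 40 × 0.25 = 30 events are expected per comparison, and only 32 of the 150 women are in the genetic-risk group. This stands and shapes the fix.

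**Conclusion.** The point holds as a matter of wording and efficiency. The endpoint is defined as a change in prevalence, but the trial is sized and tested on 12-month prevalence without baseline or strata. The analysis is valid and has the same expected between-arm difference, so this does not threaten the trial's conclusions. The forgone precision is worth about 0 to 6 power points at 40 evaluable women per arm, assuming 50% baseline prevalence and φ from 0 to 0.5. Any further gain from the strata is unknown. Ignoring them usually makes a test slightly conservative, and only if they are prognostic. The mismatch should not be resolved by testing raw change, which would cost power across the range examined. The change is worth making because it is nearly free, not because the present test is wrong.

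**What to change.** Before the code is broken:

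1. Word the primary endpoint identically in the Abstract, Design overview and statistical sections, as 12-month prevalence compared between arms with adjustment for baseline status. State whether the time point after cessation is primary; if not, remove it from the primary definition.
2. For both atypia and Ki-67, make primary a one-sided comparison of each drug with placebo, adjusted for baseline status, menopausal status, risk group and centre. Use a main-effects logistic model reported as a standardised risk difference. Name in advance the fallback for sparse data: CMH stratified on baseline status.
3. Keep women with a missing or inadequate baseline sample through a separate missing category, not complete-case deletion.
4. Report the Pearson chi-square as supportive.

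Cost: no new data and a little more analysis work. If baseline turns out not to be prognostic, the loss is under one power point in the settings examined (0.3 with full baseline data; 86.1 − 85.3 = 0.8 with 20% missing). Sparse cells are the main practical risk, hence main effects only and a stated fallback. According to the Blinding section, the code stays closed until recruitment, data collection and laboratory work are complete. The Discussion places the endpoint analysis in the future, so at the time of the article the change could still be made.

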### Randomisation

A randomization list is prepared using permuted blocks to ensure that an equal number of subjects are assigned to the 3 arms at different points of the randomization process. Neither the investigators involved with the study nor the women participating know which type of preparation is administered. The treatment and pertinent arm to which a patient has been allocated is made known only in the case of proven need (e.g., severe adverse events) by the Data Center upon formal written authorization of the Principal Investigator.

### Blinding

All participants, those who administer the therapy and those who assess the outcomes are blinded to group assignment to ensure the double blind design. Both nimesulide and simvastatin have been purchased from the market, placebo capsules have been prepared by the Hospital Pharmacy of the European Institute of Oncology (EIO). All the treatments are blinded by over-encapsulation and appear as capsules (size 0) of the same colour and exactly identical. Drug or placebo are provided in boxes (of identical shape) containing the capsules needed for each semester. They are manufactured by the EIO pharmacy. The code will be revealed to researchers and participant once recruitment, data collection, and laboratory analyses are complete.

### Recruitment and preliminary results

Among the 528 women evaluated for protocol inclusion, 388 were eligible according to inclusion criteria characteristics. The flow diagram of study of the randomized trial is shown in Figure 4. The accrual phase ended in 2011, with the randomization of the planned 150 subjects: 68 ER negative DIN, 50 LIN and AH and 32 subjects with BRCA1 mutation or high mutation probability. So far 125 women have completed the study. Ductal lavage has shown to be a feasible and reproducible procedure (only 7 patients who underwent DL at baseline shifted to FNA at 12 months). The treatment is very well tolerated and the safety blood tests did not show any significant liver toxicity, only few grade 1 for one of the liver enzymes. Only few subjects had CPK alteration with grade 1 toxicity. One case was included in the study with a baseline level of CPK grade 2 by mistake and the patient was withdrawn from the study. Including this last case, five subjects dropped out: two for gastrointestinal symptoms, one for muscle ache, and one refused to continue.

**Figure 4 F4:**
[figure not shown]
Number of subject for each phase of the randomized trial.

## Discussion

The success of chemopreventive approach depends on the recognition of high-risk subjects, the development of novel and safe agents, and the identification of new surrogate endpoint biomarkers using molecular pathways and new targets of drugs activity. Several chemoprevention studies have demonstrated that it is possible to reduce the incidence of hormone receptor positive breast cancer and that chemoprevention is clinically safe and well tolerated. Unfortunately we have no effective agents to prevent ER-negative breast cancer which accounts for 20–30% of breast cancers and has a poor prognosis [27]. Thus, it is worth identifying biomarkers and agents that are effective in the treatment and prevention of these subtypes. Several classes of new agents modulating the non-endocrine biochemical pathways have been developed and many of these are still currently under investigation. These agents include retinoids, epidermal growth factor receptor (EGFR), tyrosine kinase inhibitors (TKIs), cyclooxygenase-2 (COX-2) inhibitors, bisphosphonates, vitamin D receptor (VDR), statins, peroxisome proliferator activated receptor (PPAR), and others [28]. Safety is a major issue to take into account, since large randomized chemo-prevention trials have shown that few serious adverse events can prevent widespread public acceptance of preventive agents despite their proven efficacy. Our preliminary results showed that the treatment is very well tolerated and the safety blood tests did not show any significant liver toxicity. Ductal lavage has been proposed as a minimally-invasive, well-tolerated tool for obtaining breast epithelial cells for cytological evaluation of breast cancer risk. However, our trial might have some limitations. Ductal lavage can be highly time consuming, restricting its utility as a high-throughput clinical method. Furthermore, the effluent lavage fluid is highly diluted, thus potentially limiting its utility in possible future biochemical analysis. In spite of consistent data on Ki67 as a prognostic marker in early breast cancer, its role in atypical cells is uncertain. Furthermore, the variation in analytical practice markedly limits the value of Ki67 in this context. We assume to start the analysis of the primary and secondary endpoints within a year. To our knowledge, this is the first randomized placebo controlled trial to evaluate the role of ductal lavage to study surrogate endpoints biomarkers and the effects of these drugs on breast carcinogenesis.
